##### Cohort follow-up

2.2.1.3.

The frontal pelvic radiographs in a standing position and MRI images of the hip joints with the lower limbs in a neutral position were taken during follow-up, and the function examination and measurements were as:
1.Visual analogue scale (VAS) and Harris hip score (HHS) was used to evaluate hip joint function. As preschool children cannot describe pain precisely, we decide to change our measurements according to your recommendation. For preschoolers who are unable to describe their specific situation, along with Harris hip score, a visual analogue scale (VAS) was also applied for the assessment of pain severity of participants (17). In order to determine VAS score, a 100-mm horizontal line without scaling was designed in which 0 was marked as “no pain in hip” and 10 was marked as “unbearable pain”. Participants were then instructed to place a vertical mark reflecting their soreness severity.2.The acetabular index, Sharp's angle, cartilaginous acetabular index, and central-edge angle were measured using frontal pelvic radiographs; the morphology of the hip joints was evaluated using the Severin classification.3.The presence of RLI was observed on T2-weighted fat-suppressed MRI sequences of the hip joints. If RLI was present, the magnitude of limbus inversion was measured at level with the center of the triangular cartilage (16) (Figure 3, schematic diagram of MRI limbus inversion degree measurement).4.MRI T1ρ mapping.

**Figure 3 F3:**
[figure not shown]
Schematic diagram of MRI limbus inversion degree measurement. “*l*” is the horizontal depth of the limbus insertion, and “*L*” is the horizontal depth of the ilium-acetabular roof. The degree of limbus inversion is *t* = *l/L *× 100%.

The application of MRI T1ρ mapping to assess the quality of the acetabular cartilage has been a research hotspot in recent years. MRI T1ρ mapping can quantitatively evaluate the proteoglycan content of articular cartilage and is a sensitive indicator for measuring proteoglycan content. The T1ρ mapping values are inversely proportional to proteoglycan content. The T1ρ mapping values of the anterior, superior, and posterior acetabular cartilage were measured on the sagittal planes passing through the medial third and the lateral third of the acetabular roof, respectively.
5.Avascular necrosis (AVN) of the femoral head was assessed based on the Kalamchi–MacEwen criteria.6.The initial magnitude of limbus inversion was measured using arthrography taken at closed reduction (Figure 4, same as the measurements on MRI).

**Figure 4 F4:**
[figure not shown]
Schematic diagram of measuring the degree of limbus inversion in arthrography. Line a is the vertical line passing through the limbus and the folded joint capsule, line b is the vertical line that fills the innermost edge of the joint space (the floor of the acetabulum), and line c is the vertical line that passes through the innermost edge of the varus limbus; “*l*” is the limbus embedded horizontal depth, “*L*” is the horizontal depth of the acetabulum. The degree of limbus inversion is *t* = l/L × 100%.

Each parameter is measured by 2 raters in respective institution. Furthermore, the reliability and consistency are also conducted.

##### Statistical analysis

2.2.1.4.

Statistical analysis was performed using SPSS 27.0 software (IBM, SPSS Inc.).
1.To ensure consistency and reliability between multicenter research samples, it is first necessary to conduct a consistency analysis on the structural data, such as age and sex, of the included cases from each center and the International Hip Dysplasia Institute (IHDI) classification using the Cohen's kappa statistic. Simultaneously, the baseline characteristics (such as structural composition and pathological severity) of the included cohorts within each center must be consistent; imbalances in baseline characteristics were corrected by increasing the sample size.2.The included patients were divided into the non-limbus inversion group (A) and the limbus inversion group based on the presence of limbus inversion at closed reduction. The limbus inversion group was then further divided into the RLI group (B) and the resolved inverted limbus group (C) according to the state at final follow-up. A combination consisting of any two of the groups was organized into cohorts. Fisher's precision probability test was used to compare the difference between the sexes and affected sides, using analysis of variance to compare the different ages between the two groups. Differences in acetabular index was compared using Student's *t*-test. Chi-square test was used to compare IHDI classification, VAS and HHS, and Severin classification at the final follow-up, and analysis of variance was used to compare the MRI T1ρ mapping values and the difference in the initial magnitude of limbus inversion between groups B and C, as well as the difference between the initial magnitude of limbus inversion and that at the final follow-up in group B.3.ROC curve analysis was used to predict the cut-off value of the initial magnitude of limbus inversion in the case of persistent RLI as well as calculate its specificity, sensitivity, and statistical significance.4.Sample size calculation.In this study, ossification of the acetabular cartilage was the main observation; thus, improvement of the acetabular index was the most suitable observation indicator. The sample size calculation was based on the previously published acetabular index at the final follow-up in the group with RLI and the group without RLI after closed reduction (21.41°±3.61° and 18.88 ° ± 4.32° in the two groups, respectively) (15). The significance level *α*, the statistical power of the test, the ratio of the sample sizes in the two groups, and the percentage of patients lost to follow-up were set at 0.05, 0.9, 1:1, and 20%, respectively. The minimum sample size for each group was calculated to be 67 cases (134 cases in total). Therefore, at least 67 cases needed to be enrolled in the observation group and the control group, respectively.

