## Introduction

1.

Closed reduction is a common method for treating developmental dysplasia of the hip (DDH) in children aged 6–8 months; however, re-dislocation after reduction, avascular necrosis, residual acetabular dysplasia (RAD), and other complications cannot be completely avoided (1). Among these, RAD is the most common complication of DDH closed reduction treatment. A prospective multicenter study conducted by Sankar et al. (2) found that even with stable closed reduction, approximately 11% of children still had residual dysplasia, and long-term follow-up results of a study by Terjesen (3) noted a higher statistic of up to 38%. RAD is the main cause of osteoarthritis (OA) in young adults (4, 5) which often requires total hip replacement (THR). Approximately 9.1% of THR is caused by RAD, and among young adults, this proportion is as high as 21%–29% (6, 7). Therefore, prevention of RAD after DDH treatment and timely correction of RAD are key to long-term prevention of OA.

The causes of RAD in children after closed reduction for DDH are complex. Age, dislocation height, and acetabular index at reduction are commonly used clinical indicators to predict RAD (3, 8, 9), but these factors can only partially explain the causes of RAD from clinical phenomena. Several factors affect the development of the acetabulum after closed reduction. In addition to the genetic quality of DDH, the quality and development potential of the acetabular cartilage, the soft tissue in the acetabulum, and the evolution of the concentric relationship between the acetabulum and femoral head are related to the shaping ability of the hip joint. A relevant understanding of the internal causes of RAD and timely intervention are of clinical significance for the prevention of OA caused by RAD. Previous clinical studies based on indirect radiological observations cannot directly reflect real world practice, in which the non-bone structure and concentric evolution of the hip joint must be considered. Radiological observations can be used to monitor acetabular development; however, they cannot accurately predict RAD (10, 11). Therefore, a method for follow-up observation of hip joint development is warranted to enable better clinical understanding of RAD.

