##### Randomized blocks and interventions

2.2.2.2.

A randomized trial study design was the most appropriate approach to observe the efficacy of surgical intervention, with blinding techniques used during statistical analysis of the data. A double-blind study was not feasible because the surgeon was required to provide detailed information on the surgical regimen. The researchers in each center divided the RLI participants into two study cohorts based on the randomized block design, i.e., the surgery and non-surgery groups. After informed consent was obtained from the guardians of patients in the surgery group, clearance of the inverted limbus *via* arthrotomy was performed.

All surgeries were performed by pediatric hip joint surgeons with senior job titles *via* a bikini incision, and the inverted limbus tissue embedded between the acetabulum and femoral head was excised after arthrotomy without damaging the limbus-cartilage complex. After surgery, casts or braces were applied to immobilize single hips in abduction for 4 weeks and the patients gradually resumed walking after removal of external fixators. No special rehabilitation therapy was administered.

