##### Statistical analysis

2.2.2.6.

Fisher's precision probability test was used to compare the difference between the sexes and affected sides, using analysis of variance to compare the different ages between the surgical and non-surgical cohorts. Differences in acetabular index was compared using Student's *t*-test. Chi-square test was used to compare IHDI classification, VAS and HHS, and Severin classification at the final follow-up, and analysis of variance was used to compare the MRI T1ρ mapping values and the incidence of Grade III and Grade IV adverse events.

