##### Cohort grouping and interventions

2.2.3.2.

For cases meeting the assessment criteria specified in 2.3.1, the labral morphology was further evaluated using intraoperative arthrograms if there was no limbus inversion or if magnitude of the limbus inversion was <32% of the horizontal depth of the acetabular roof (or the cut-off value obtained in 2.2.1). A closed reduction using Spica cast immobilization was then performed to construct the control cohort. If intraoperative evaluation suggested that the magnitude of limbus inversion exceeded the cut-off, open reduction with post-reduction Spica cast immobilization was performed, in which the acetabular soft tissues were removed *via* the bikini incision approach, and the inverted limbus was excised. Patients undergoing open reduction procedures constituted the experimental cohort. Patients in the two cohorts underwent post-reduction cast immobilization for 3 months followed by immobilization with braces for 3 months.

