At present, the changes and outcomes of the inverted limbus after closed reduction of DDH remain controversial. Severin et al. (23) believed that after achieving stable closed reduction, the inverted limbus would be gradually absorbed and disappear; however, others believed that the inverted limbus was a key factor leading to AVN. Previous studies have been based on indirect observation of x-ray images, and there is a lack of direct evidence regarding the morphological evolution of the inverted limbus. This study used serial MRIs to observe the outcomes of limbus inversion after closed reduction of DDH, which lessened the impact of radiation on pediatric patients and enhanced the safety and reliability of the study. Our previous findings indicated that the magnitude of limbus inversion after closed reduction is closely related to its medium-term morphological outcome (16). However, the previous study had certain limitations since it was based on a small sample and did not follow-up until skeletal maturity. Previous studies have confirmed that a primary limbus inversion leads to primary acetabular dysplasia and early-onset OA (24, 25), but the long-term result of RLI has not been reported in DDH patients who previously underwent closed reduction.

Reaching skeletal maturity of the hip is a long-term process; therefore, the prospective design of this protocol better reflects the relationship between RLI and multiple prognostic outcomes while balancing many known or unknown biases. This research plan is to be led by the corresponding author's institution and carried out by multiple clinical research centers in cooperation with pediatric orthopedic centers in China. Compared to previous case-control studies, this study was designed as a multicenter clinical study with a higher level of evidence. Consistency of the characteristics included in a multicenter sample study is a key issue in clinical research. In the process of sample collection, cohort characteristics within each center are required to achieve homogeneity, which can be solved by increasing the sample size to ensure reliability of the final pooled samples. The follow-up rates in clinical studies are another key issue affecting reliability of the study results. Specialized staff in each center were assigned the task of following included cases, establishing case study databases, and recording various contact methods to guarantee a follow-up rate of over 80%.

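### Baseline imbalance is to be cured by a larger sample, while the two non-randomised parts compare acetabular index by an unadjusted t-test

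*Protocol article*

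**What the plan says.** **Remedy for imbalance.** Section 2.2.1.4, item 1, asks for consistent baseline characteristics within each centre and says that "imbalances in baseline characteristics were corrected by increasing the sample size". The Discussion treats homogeneity of the centre cohorts as a problem "which can be solved by increasing the sample size to ensure reliability of the final pooled samples".

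**Consistency check.** The same item names age, sex and "the International Hip Dysplasia Institute (IHDI) classification using the Cohen's kappa statistic". Section 2.2.2.5 carries this check into part 2 as bias control.

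**Test for AI.** Sections 2.2.1.4, 2.2.2.6 and 2.2.3.4 use the same words: "Differences in acetabular index was compared using Student's" t-test. Sex, side, age and IHDI class are only tested for difference. The article names no regression, matching, stratified or propensity method.

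**How groups arise.**
- Part 1: patients are split by limbus inversion at reduction, and those with inversion are "further divided into the RLI group (B) and the resolved inverted limbus group (C) according to the state at final follow-up".
- Part 3: "If intraoperative evaluation suggested that the magnitude of limbus inversion exceeded the cut-off, open reduction with post-reduction Spica cast immobilization was performed"; the other eligible patients form the control cohort.
- Part 2: patients are allocated within centres "based on the randomized block design".

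**Known predictors.** The Introduction states: "Age, dislocation height, and acetabular index at reduction are commonly used clinical indicators to predict RAD".

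**The concern.** Groups formed by limbus state (part 1) or by inversion magnitude (part 3) can be expected to differ in the severity of the original dislocation. Such a difference belongs to the populations compared. Recruiting more of the same patients estimates it more precisely but does not shrink it. An unadjusted t-test passes its effect on AI straight into the result.

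Section 2.1 gives the impact of residual limbus inversion (RLI) on acetabular development as the main purpose, and the results are meant to inform indications for surgery. A severity difference mistaken for an effect of RLI would feed into those indications, and following the stated rule would make the mistake look more certain.

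The kappa check offers no protection. Kappa measures agreement between ratings of the same subjects, so it cannot show whether different patients at different centres are alike in age or sex.

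**Working it through.** **1. The plan's own figure.** Section 2.2.1.4 gives final AI of 21.41° (SD 3.61) and 18.88° (SD 4.32), α 0.05, power 0.90, ratio 1:1 and 20% loss. Sidedness is not stated; two-sided reproduces the result.
- Difference: 21.41 − 18.88 = 2.53°.
- Sum of variances: 3.61² + 4.32² = 13.03 + 18.66 = 31.69.
- n = (1.960 + 1.282)² × 31.69 / 2.53² = 52.03, so 53 evaluable per group.
- 53 / 0.8 = 66.25, so 67 per group. This matches the article and is not in dispute.

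**2. What a larger sample does to a fixed bias.** Assume no true effect and 1° of confounding, which is 1/2.53 = 40% of the planned difference. With SE = √(31.69/n), the rejection probability is Φ(1/SE − 1.96) + Φ(−1/SE − 1.96).

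| n per group | SE | 1/SE | Rejection at nominal 5% |
|---|---|---|---|
| 53 | 0.773° | 1.29 | 25% |
| 134 | 0.486° | 2.06 | 54% |
| 268 | 0.344° | 2.91 | 83% |

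The bias is 1° in every row; only the standard error falls.

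**3. Where 1° could come from.** If baseline and final AI have equal SDs and correlation ρ, an unadjusted comparison of final AI is biased by ρ × the baseline difference. The article gives neither quantity. A 2° baseline difference with ρ = 0.5 gives 1.0°. Over baseline differences of 1° to 3° and ρ of 0.3 to 0.7, the bias runs from 0.3° to 2.1°, and the false-positive rate at 53 per group from 7% to 78%.

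**4. Simulation** (2,000 runs, 2° baseline difference, ρ = 0.5, no true effect).

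| n per group | Unadjusted t-test | Baseline AI in the model |
|---|---|---|
| 53 | 26% | 5.9% |
| 212 | 73% | 4.8% |

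In this set-up adjustment restores the error rate, and quadrupling the sample makes it worse.

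**5. Part 2.** Randomisation removes systematic imbalance, so the question is precision. Including entry AI multiplies the variance by 1 − ρ². For an assumed ρ of 0.3 to 0.6 this is 0.91 to 0.64, a cut of 9% to 36%. If blocks or centres explain 5%, 10% or 20% of the variance (assumed), ignoring them makes the nominal 5% test run at 4.4%, 3.9% or 2.8%, which is conservative.

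**The case against.** **Detail may sit elsewhere.** Section 4.2 mentions a data analysis plan and an independent statistical team. That would answer a mere omission. Here the article names both the test and the remedy, so a later plan would have to contradict it.

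**The rule may concern centres or chance.** The sentence speaks of cohorts within each centre, and chance imbalance does shrink with n. But enlarging the sample corrects systematic differences neither between centres nor between groups. If selective recruitment to balance groups was meant, no matching rule is given.

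**Design restriction already helps.** Section 2.2.1.1 limits age at reduction to 6–18 months, excludes earlier treatment and fixes the immobilisation. This narrows some confounding, age above all, but leaves dislocation height and AI at reduction open. The 1° is an assumption and could be smaller.

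**Kappa may refer to IHDI only.** IHDI is a rated grade and section 2.2.1.3 has two raters, so this reading is possible. The sentence nevertheless lists age and sex under the same check and needs rewording.

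**The randomised part.** A reader might infer that the t-test there is biased or throws away baseline AI. The documents do not support that. The test is valid under randomisation, and sections 2.2.1.4 and 2.3.1 speak of improvement in AI, so a change score, which uses baseline AI, may be what is tested.

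**Sample size.** A reader might also infer that testing improvement leaves the trial too small. With equal SDs and an unchanged 2.53° difference, a change score needs 52.03 × 2(1 − ρ) per group: 72.8 at ρ = 0.3, 52.0 at 0.5 and 41.6 at 0.6. The answer turns on an unknown correlation, and 53 belongs to part 1; the article states no sample size for part 2. No shortfall is shown.

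**Conclusion.** The stated rule is wrong as written for parts 1 and 3. A larger sample leaves systematic imbalance where it is, and with the unadjusted t-test it raises the chance of a false finding: 25%, 54% and 83% at 53, 134 and 268 per group under an assumed 1° bias and no true effect. The direction of this result needs only a non-zero systematic imbalance in a predictor of AI. The size rests on the assumed bias and the article's own SDs.

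Three limits apply. In part 2 the issue is efficiency, not validity. In part 3 the cut-off puts patients with large and small inversion in different treatment groups, so no covariate model can separate clearance from severity of inversion. And it should not be inferred that every covariate is in hand: section 2.2.1.3 lists AI on follow-up radiographs, and the only measure it places at reduction is limbus inversion on arthrography.

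**What to change.** 1. Delete the sample-size remedy in section 2.2.1.4, item 1, and in the Discussion.
2. In parts 1 and 3, replace the t-test by a linear model for AI with group, age at reduction, IHDI grade, centre and follow-up time, plus AI at reduction where that radiograph is available. Say how patients without it are handled.
3. In part 3, state that inversion magnitude determines treatment and that adjustment cannot separate the effect of clearance from severity of inversion.
4. Restrict kappa to agreement of raters on the same images, and describe case-mix by centre in tables.
5. Optional, part 2: analyse AI at a fixed time point by ANCOVA with entry AI and block or centre.

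**Cost.** Mostly analysis wording, with no change to recruitment or treatment. The one possible data cost is retrieving AI at reduction for parts 1 and 3, which the article does not explicitly list as collected. Entry AI for part 2 is measured under sections 2.2.2.1.1 and 2.2.2.1.2.

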##### Bias control

2.2.2.5.

To control bias as much as possible, blinding techniques were adopted for data measurement and analysis, i.e., after the imaging data from each center were summarized into research groups, the grouping of clinical data was blinded to the data measurers; at the same time, a consistency test was conducted on the basic situation of the cohort composition within each center (in the same manner as study protocol 2.2.1) to control bias caused by differences in sample composition at different centers.

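### In the non-randomised part 1, enlarging the sample is given as the correction for baseline imbalance, but it leaves systematic imbalance between the groups untouched and only tightens the interval around a biased difference

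*Protocol article*

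**What the plan says.** Protocol article, 2.2.1.4 Statistical analysis, item 1, requires that "the baseline characteristics (such as structural composition and pathological severity) of the included cohorts within each center must be consistent" and then states that "imbalances in baseline characteristics were corrected by increasing the sample size". The Discussion says the same of the programme as a whole: "cohort characteristics within each center are required to achieve homogeneity, which can be solved by increasing the sample size".

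Item 2 of 2.2.1.4 forms the part 1 groups. Children are first split "based on the presence of limbus inversion at closed reduction", which gives group A (no inversion) and an inversion group. The latter is then "divided into the RLI group (B) and the resolved inverted limbus group (C) according to the state at final follow-up". Cohorts are pairs of these groups: "A combination consisting of any two of the groups was organized into cohorts". The analysis of the main measure is one sentence: "Differences in acetabular index was compared using Student's *t*-test".

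None of the three statistical sections (2.2.1.4, 2.2.2.6, 2.2.3.4) names regression adjustment, matching, weighting or stratification. The Introduction lists age, dislocation height and acetabular index at reduction as the usual clinical predictors of residual acetabular dysplasia (RAD).

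**The concern.** A larger sample reduces random error. It does not change a difference that is built into how the groups arise. If children whose limbus stays inverted were on average older or more severely dislocated at reduction, the next hundred children from the same clinics would show the same pattern. By the protocol's own account these characteristics predict RAD, so such an imbalance would carry over into the acetabular index at final follow-up.

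The stated rule therefore does not do what it claims, and it makes the inference worse: the biased difference stays and its standard error falls. Part 1 also matters for what follows. Its cut-off for limbus inversion may set eligibility in part 2 (2.2.2.1.1, criterion 8) and decides between closed and open reduction in part 3 (2.2.3.2). An association in part 1 that reflects case mix would weaken the rationale for both.

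**Working it through.** **Inputs from 2.2.1.4 item 4.** Acetabular index 21.41 (SD 3.61) with residual limbus inversion and 18.88 (SD 4.32) without; alpha 0.05; power 0.9; ratio 1:1; loss 20%; stated result 67 per group, 134 in total.

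**Step 1: reproduce the plan's figure.**
- Difference = 21.41 − 18.88 = 2.53 degrees.
- Pooled SD = √[(3.61² + 4.32²)/2] = √15.847 = 3.98 degrees.
- n per group = 2 × (1.960 + 1.282)² × 15.847 / 2.53² = 52.03, rounded up to 53 (two-sided test).
- Allowing for loss: 53/0.8 = 66.25, rounded up to 67.

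The stated 67 per group is reproduced, so the sample size is not in dispute.

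**Step 2: what a larger n does to a fixed bias.** Suppose there is no true difference, but case mix shifts the unadjusted group difference by b degrees. The expected difference is b at every n. The standard error is 3.98 × √(2/n), and the rejection rate of the two-sided 5% t-test follows from the noncentral t distribution with noncentrality b/SE. The values of b are assumptions, all below the planning difference of 2.53.

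| n per group | SE | 95% half-width (1.96 × SE) | False positives, b = 0.5 | b = 1.0 | b = 1.5 |
|---|---|---|---|---|---|
| 67 | 0.688 | 1.35 | 11% | 30% | 58% |
| 134 | 0.486 | 0.95 | 18% | 54% | 87% |
| 268 | 0.344 | 0.67 | 31% | 83% | 99% |

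A normal approximation agrees to within one percentage point (31% instead of 30% for b = 1.0 at 67 per group, 59% instead of 58% for b = 1.5). The sizes 134 and 268 are simply twice and four times the plan's minimum; the protocol does not announce them.

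**Step 3: does the baseline imbalance itself shrink?** Assume the groups truly differ by 0.3 SD on a baseline severity measure. At 67, 134 and 268 per group the expected standardised difference stays at 0.30, and only its sampling SD falls (0.17, 0.12, 0.09). Under randomisation the true difference is zero, and the expected absolute chance imbalance, √(2/n) × √(2/π), does fall: 0.14, 0.10, 0.07. The remedy works for chance imbalance and fails for systematic imbalance, and in part 1 systematic imbalance is the kind to worry about.

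**The case against.** **The sentence may be about centres.** Item 1 opens with consistency between centres, and the Discussion places the remedy under homogeneity of a multicentre sample. Small centre samples do vary by chance, and that part shrinks with n. This stands as far as it goes. But the clause speaks of cohorts inside a centre, item 2 defines cohorts as pairs of groups A, B and C, and a systematic difference in case mix between centres would not shrink either. The remedy fails on both readings.

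**Design controls exist.** Restriction to reduction at 6–18 months, no other prior treatment, a common cast and brace course, and exclusion of neuromuscular or syndromic cases all reduce confounding. They do not remove differences in age or severity within those limits.

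**A covariate model can be left to an analysis plan.** Agreed, and its absence from the article is not the point. The point is a remedy that the article states and that is wrong.

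**Stronger readings that the text does not support.**
- A reader might infer that the randomised part would be enlarged in the same way. Section 2.2.2.5 says only that "a consistency test was conducted on the basic situation of the cohort composition within each center (in the same manner as study protocol 2.2.1"). That carries over the check, not the enlargement, and chance imbalance under randomisation does shrink with n.
- A reader might infer that the rule has no end, because a larger sample makes a baseline test flag the same difference more often. That needs a significance trigger, and the protocol states none; the method it names for the consistency check is Cohen's kappa.
- A reader might infer that error is inflated because the sample size depends on looks at the data. The looks described are at baseline composition, not at outcome, and no inflation from them has been shown. The 67 is also worded as a minimum, so exceeding it is not a departure from the plan.

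**Conclusion.** The concern holds for part 1. Increasing the sample size is stated as the correction for baseline imbalance in 2.2.1.4 item 1 and again in the Discussion. For groups that form naturally and are compared by an unadjusted t-test, it cannot remove systematic confounding, and it raises the chance that the bias is declared a finding. The direction holds for any non-zero bias. The size is illustrative: with no true effect and an SD of 3.98, an assumed bias of 0.5 degree gives 11%, 18% and 31% false positives at 67, 134 and 268 per group, and 1.0 degree gives 30%, 54% and 83%. The documents supply no bias size, so these are not estimates of this study's error rate.

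The same reasoning applies to part 3 (2.2.3.4), where the cohorts are set by the degree of inversion and are also compared without adjustment. It does not make section 2.2.2.5 of the randomised part an error.

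**What to change.** - Delete the clause on enlarging the sample in 2.2.1.4 item 1 and its counterpart in the Discussion. Keep 67 per group as the minimum size for power.
- In 2.2.1.4 item 2, replace the unadjusted comparison of acetabular index by a regression (or a stratified analysis) adjusted for age at reduction, IHDI grade or dislocation height, acetabular index at reduction, and centre. Acetabular index at reduction belongs on the list because the Introduction names it as a predictor of RAD and it is the starting value of the outcome measure. Adjustment deals only with what has been measured, and the text should say so.
- Make the matching change for the non-randomised comparison in 2.2.3.4.
- Optional: add to 2.2.2.5 that enrolment in the randomised part will not be extended because of observed baseline differences. This is a clarification, not a correction.

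The cost is a change of wording and a little more analysis work. Age and IHDI class are already compared in part 1; acetabular index and centre have to be available at the time of reduction for each child.
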